# Study protocol: a randomised controlled trial of a nurse-led community-based self-management programme for improving recovery among community-residing stroke survivors

**DOI:** 10.1186/s12913-016-1642-9

**Published:** 2016-08-15

**Keywords:** Stroke, Disease management, Self-efficacy, Community-dwelling, Quality of life, Community reintegration, Randomised controlled trial

## Abstract

**Background:**

Recovery after stroke is long-term and demanding. Optimising community-residing stroke survivors’ capability to self-manage their health is integral. Recent systematic reviews have shown that stroke self-management programmes were associated with significant improvement in stroke survivors’ health-related quality of life and self-efficacy. However some programmes were not designed with an underpinning theoretical framework. The aim of this study is to compare the effectiveness of a nurse-led stroke self-management programme with usual care on recovery of community-residing stroke survivors.

**Methods/Design:**

A single-blinded, two-arm, randomised controlled trial will be conducted. Patients with a history of first or recurrent ischaemic or haemorrhagic stroke who will be discharged to home settings will be recruited from acute stroke units of three acute public hospitals in Hong Kong. The estimated sample size is 160 (80 participants per group). Eligible participants will be randomised to receive either usual care or a 4-week nurse-led community-based self-management programme plus usual care after discharge. The programme, underpinned by Bandura’s constructs of self-efficacy and outcome expectation, includes one individual home visit, two community-based group sessions, and three follow-up phone calls. Primary outcomes include stroke survivors’ self-efficacy and outcome expectation of performing self-management behaviours. Secondary outcomes include health-related quality of life, satisfaction with performance of self-management behaviours, depressive symptoms, and community reintegration. Participants will be assessed at baseline and at 8 weeks after randomisation. Generalised estimating equations will be performed to evaluate the significance of changes in outcomes over time by treatment condition. Research ethics approvals were obtained.

**Discussion:**

It is expected that stroke survivors receiving the stroke self-management programme will have improved self-efficacy, outcome expectation, and performance of stroke self-management behaviours. Enhanced quality of life and level of community reintegration, and decreased depressive symptoms are also expected. The study results will provide valuable evidence to inform future identification and evaluation of best approach to deliver stroke self-management programmes to enhance community-residing stroke survivors’ recovery.

**Trial registration:**

ClinicalTrials.gov identifier: NCT02112955; date of registration: 09/04/2014

## Background

Stroke is the second leading cause of global death with the death toll amounting to 6.7 million (11.9 % of all deaths) in 2012 [1]. In Hong Kong, stroke was the fourth leading cause of death in 2014 [2]. Stroke is a significant cause of disability with survivors having a higher risk of depressive symptoms and a lowered quality of life [3]. Indeed stroke recovery is long-term and demanding, encompassing not only physical rehabilitation, but also coping with cyclic frustrations and adapting to new life roles [4, 5]. Previous studies found poorer functional ability, more depressive symptoms, and lower self-esteem were significantly associated with participation restriction 12 months post-stroke [6]. The period for optimal recovery inevitably extended far beyond in-patient rehabilitation. The level of complexity in managing physical and psychosocial needs after stroke is intensified when stroke survivors return home and healthcare professionals are not immediately available to provide support. Furthermore when at home support from family may decrease as they return to their normal life [7]. Provision of effective community-based interventions to optimise stroke survivors’ capability to manage their post-stroke challenges is important to foster independence and early reintegration to pre-stroke life.

Self-management refers to an individual’s active participation in managing the symptoms, treatment, physical and psychosocial consequences of a chronic illness. There are three main components of chronic disease self-management including medical, emotional and role management [8]. To attain effective self-management, practicing core self-management skills including goal-setting, problem-solving, decision-making, resources utilisation and communication with healthcare professionals is crucial [4]. A recent systematic review of nine randomised and six non-randomised studies reported benefits of stroke self-management programmes in physical outcomes, quality of life, and confidence in recovery among stroke survivors. However the essential contents and the best approach to deliver the programmes for stroke survivors are yet to be determined [9].

Stroke self-management programmes are complex interventions given the interaction of multiple components of interventions with varying strengths, doses, or contents. According to the Medical Research Council guidance [10], designing complex interventions with an underlying theoretical premise enables its systematic development and implementation, and informs selection of appropriate outcome indicators. Furthermore it helps predict and explain the mechanism of change in target behaviours or the relationship between interventions and outcomes. A recent systematic review was conducted to examine the effectiveness of theory-based stroke self-management programmes [11]. The review included three randomised controlled trials examining three community-based programmes based on the Stanford Chronic Disease Self-management programme underpinned by Bandura’s construct of self-efficacy. The results showed potential benefits of the programmes in improving stroke survivors’ self-efficacy and health-related quality of life. However only two of the three included studies explicitly described how the theory informed programme design and implementation, and measured stroke survivors’ changes in self-efficacy. The other study neither linked the programme to Bandura’s four sources of self-efficacy nor measured self-efficacy [11]. There is also insufficient evidence on effectiveness of different strategies to enhance community-residing stroke survivors’ self-efficacy in managing their health conditions. All studies were conducted in Western countries and were delivered by healthcare professionals or trained peer leaders [11]. There has been no study which assessed the effectiveness of stroke self-management programmes delivered by nurses for Chinese stroke survivors.

In Hong Kong, stroke patients, after having their acute medical conditions stabilised, are either transferred to rehabilitation hospitals for continued rehabilitation, or discharged directly to their homes, old aged homes or other residential care homes depending on their progress. Community-based support for stroke survivors, particularly for those after returning home, often includes stroke support groups, private physiotherapy or occupational therapy, and social services offered by non-government organisations such as vocational training. However, support programmes for community-residing stroke survivors to promote their psychological and social well-being, as well as to enhance their knowledge and skills for better reintegration into the community and assumption of post-stroke social and life roles are relatively insufficient. Given the potential programme benefits, it would be worthwhile to determine the effectiveness of a community-based nurse-led stroke self-management programme underpinned by a theoretical framework for Chinese stroke survivors. The findings of such a study would inform future identification and evaluation of best strategies to deliver effective stroke self-management programmes.

### Research aim

To examine the effectiveness of a nurse-led community-based self-management programme for improving recovery among Chinese community-residing stroke survivors.

### Research objectives

To determine the effectiveness of the programme on improving community-residing stroke survivors’self-efficacy, outcome expectation, and satisfaction with performance of self-management behaviours;health-related quality of life;depressive symptoms; andcommunity reintegration.

## Methods/Design

### Study design and setting

A two-arm, single-blinded randomised controlled will be conducted (Fig. 1). Participants will be recruited from acute stroke units of three public hospitals in Hong Kong. The nurse-led community-based self-management programme will be conducted at both the participants’ homes and a community centre after the participants have been discharged home from the hospital.

**Fig. 1 Fig1:**
[figure not shown]
Study design and flow of participants

### Ethics consideration

Ethical approvals have been obtained from the Kowloon West Cluster Research Ethics Committee, Hospital Authority, Hong Kong (Ethical Approval No.: KW/EX-14-021(71–21)), the Joint Chinese University of Hong Kong-New Territories East Cluster Clinical Research Ethics Committee, Hong Kong (CREC Ref. No.: 2014.375-T), and the Human Research Ethics Committee of the Queensland University of Technology (Approval No.: 1400000333). Written informed consent will be collected from participants before commencing data collection. All potential participants will receive a full explanation by the research assistant about the purpose and data collection process of the study, their rights to voluntarily participate, refuse, or withdraw from the study without any negative consequences to them. The questionnaires will be anonymous and will be used for research purposes only. All the information collected will be kept strictly confidential and will be destroyed six years after completion of the study. The federal and institutional ethical standards, Hong Kong Personal Data (Privacy) Ordinance, Declaration of Helsinki, and ICH-GCP will be upheld.

### Participants

All stroke survivors admitted to the acute stroke units will be recruited if they 1) are aged 18 years or above; 2) have a clinical diagnosis of a first or recurrent ischaemic or haemorrhagic stroke (inclusive of intracerebral haemorrhage and subarachnoid haemorrhage); 3) will be discharged from hospital to home in the next seven days; 4) have a Mini Mental State Examination (MMSE) score >18 measured at the time of consenting to participate in the study [12]; 5) can speak Cantonese; and 6) can attend sessions of the self-management programme.

Participants will be excluded if they 1) are diagnosed with transient ischaemic attack, subdural or epidural haemorrhage [13]; 2) have cerebrovascular events due to malignancy or head trauma; 3) have limited comprehension and receptive aphasia; 4) have been diagnosed with schizophrenia, bipolar disorder, or dementia; or 5) have received a stroke self-management programme in the past 12 months.

### Sample size estimation

Primary outcome of this trial is stroke survivors’ self-efficacy in performing self-management behaviours measured by the Stroke Self-Efficacy Questionnaire at eight weeks after randomisation. A sample size of 64 per group (128 for two groups) is required to detect a significant mean difference in self-efficacy between groups for a medium effect size of 0.5 [14] with significance set at 0.05 and a power of 0.8 [15]. Taking into consideration an attrition rate of 19 % over six months among stroke survivors [14], the final sample size is 160 (80 participants per group). Recruitment of participants is anticipated to take 12 months.

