### Outcome measures

#### Primary outcomes

##### Self-efficacy

The 13-item Stroke Self-Efficacy Questionnaire (SSEQ) will be used to measure participants’ self-efficacy in performing daily functional activities and self-management such as getting in or out of bed, preparing meals, or persevering to make progress [18]. Each item is rated on an 11-point Likert scale (0 = ‘not at all confident’; 10 = ‘very confident’). The score of all items is summed to yield the total score (range 0–130). A higher score represents higher self-efficacy in performing daily functional activities and self-management. The authors have back-translated [19] and validated the Chinese version of SSEQ in a convenience sample of 135 Chinese community-residing stroke survivors. The results showed high internal consistency (Cronbach’s alpha = 0.92). There were positive correlations between the total scores of the translated Chinese version of SSEQ, and General Self-Efficacy Scale (Spearman’s rho *r*_*s*_ = 0.48, *p* < 0.01) and Frenchay Activities Index (Spearman’s rho *r*_*s*_ = 0.51, *p* < 0.01), suggesting acceptable convergent validity.

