##### Outcome expectation

An 11-item Chinese version of the Stroke Self-management Outcome Expectation Scale was developed based on Bandura’s construct of self-efficacy [16], and previous literatures on stroke self-management [4] and outcome expectation [20, 21] to measure participants’ current level of confidence that the desired outcomes will be resulted after performing the self-management behaviours. Each item is rated on an 11-point Likert scale (0 = ‘not confident at all’; 10 = ‘very confident’). The total score is summed (range 0–110). A higher score indicates higher confidence in likelihood of the outcomes to occur. An expert panel of two nurse academics, one nurse manager, three advanced practice nurses and two physicians performed assessment of content validity (Content validity index: 0.98). The scale was piloted in a convenience sample of 83 Chinese community-residing stroke survivors and showed high internal consistency (Cronbach’s alpha = 0.94).

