### Data collection procedures

All potential participants will be identified by reviewing their medical records or referrals by stroke nurses at the study venues. The principal investigator or research assistants will screen the participants in a face-to-face interview for their eligibility and willingness to participate in the study. Written informed consent will be obtained from those who are eligible. A card indicating participants’ involvement in the study and means of urgent contact will be provided to each participant after obtaining the consent. The consented participants’ demographic and clinical information will be retrieved from their medical records. Baseline and follow-up assessments will be conducted by two research assistants. The participants will be scheduled via phone by a research assistant for baseline assessment within one month after their discharge from hospital. Immediately after baseline assessment is completed, the participants will be randomly assigned to either the intervention or the control group. At 8 weeks after randomisation, the participants will be scheduled via phone by the research assistant again for follow-up assessment. The research assistants will administer the assessment tools in a face-to-face interview at the participants’ homes. The administration of the questionnaires has been pilot tested among six Chinese community-dwelling stroke survivors (mean age 55 years, SD 10.35, range 35–64 years). It took an average of one hour to complete the six questionnaires. Another research assistant will call the participants in the intervention and control groups at the time immediately after programme completion to collect their feedback on the programme (Table 3). The research assistants will be trained to administer the assessment tools consistently and non-judgmentally; and be reminded of the importance of confidentiality and safe storage of data. Inter-rater reliability between research assistants will be checked using Kappa statistics before data collection.

**Table 3 Tab3:** Summary of measurements and study outcomes

Measurements	Instruments	Group	Baseline	Follow-up	Outcomes	
					1°	2°
Self-efficacy	SSEQ	IG, UG	×	×	×	
Outcome expectation	SSOES	IG, UG	×	×	×	
Satisfaction with performance of SSMB	SSBPS	IG, UG	×	×		×
Health-related quality of life	SSQOL	IG, UG	×	×		×
Depressive symptoms	GDS	IG, UG	×	×		×
Community reintegration	RNLI	IG, UG	×	×		×

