### Statistical analysis

Statistical analyses will be performed using the IBM SPSS Statistics version 22 (SPSS Inc., Chicago, IL, USA). All primary analyses will be conducted on an intention-to-treat basis. No interim analyses will be undertaken. Descriptive statistics will be used to summarise participants’ baseline characteristics and outcome variables. All continuous outcomes will be assessed for normality in distribution. Appropriate transformation of skewed data will be performed before analysis. Chi-square tests and independent t-tests will be used to compare the demographic and clinical characteristics, and mean scores of outcomes between the intervention and control groups at baseline. A generalised estimating equation (GEE) model will be employed to assess differential change of the primary and secondary outcomes across the time points (baseline and eight weeks after randomisation) between the two groups. Adjustment will be made for potential confounding demographic and clinical variables, including gender, age, number of strokes, NIHSS, and the Barthel ADL Index, that were ‘unbalanced’ between the two groups (*p* < 0.25) [31, 32]. The longitudinal association of self-efficacy and outcome expectation with secondary outcomes will be examined using GEE model. GEE model can account for intra-correlated repeated measures data and accommodate missing data caused by dropouts, provided the data are missing at random [33], and is particularly suitable for intention-to-treat analysis without imputation for missing data. Significance level will be set at two-sided *p* < 0.05 and all statistical tests will be two-tailed.

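### The protocol names one primary outcome in the sample size section and two elsewhere; the stated 80% power covers only the first, and the 5% error rate depends on which is meant and how success is judged

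*Protocol article*

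**What the plan says.** Four places in the protocol article say which outcomes are primary.

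- **Sample size estimation** uses the singular: "Primary outcome of this trial is stroke survivors’ self-efficacy in performing self-management behaviours measured by the Stroke Self-Efficacy Questionnaire at eight weeks after randomisation". The effect size of 0.5, the 0.05 significance level, the power of 0.8 and the final 160 participants all refer to self-efficacy.
- **Abstract, Methods/Design** uses the plural: "Primary outcomes include stroke survivors’ self-efficacy and outcome expectation of performing self-management behaviours".
- **Outcome measures** has the heading "Primary outcomes". Under it come self-efficacy (the Stroke Self-Efficacy Questionnaire, SSEQ) and then outcome expectation (the Stroke Self-management Outcome Expectation Scale, SSOES). The secondary outcomes heading follows only after both.
- **Table 3**, titled "Summary of measurements and study outcomes", marks both SSEQ and SSOES in the primary column.

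The Statistical analysis section uses a generalised estimating equation model "to assess differential change of the primary and secondary outcomes across the time points". It then sets one level for everything: "Significance level will be set at two-sided *p* < 0.05 and all statistical tests will be two-tailed".

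**The concern.** The primary outcome decides what counts as a positive trial and what the sample size supports. Here one section fixes a single outcome and three others fix two, so the article supports two definitions of success.

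Suppose SSEQ shows no effect and SSOES does. On the sample size section's definition the trial is negative. On the abstract and Table 3 it could be presented as positive on a primary outcome, although no effect size or power is stated for SSOES. If the conflict stays open until the results are known, the choice can follow the data.

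The nominal 5% error rate and the 80% power are attached to the single-outcome definition. Whether they also hold with two primary outcomes depends on how the two results are combined.

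**Working it through.** **Inputs.** From Sample size estimation: standardised difference 0.5, alpha 0.05, power 0.80, 64 per group before attrition, 19% attrition, 80 per group (160 in total) after it. From Statistical analysis: two-sided 0.05. The correlation between the SSEQ and SSOES test statistics is not given and is varied below as an assumption.

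**1. The plan's own sample size.** The normal approximation is n = 2(z₀.₉₇₅ + z₀.₈₀)²/d² = 2(1.960 + 0.842)²/0.5² = 62.8, so 63 per group. The noncentral t calculation gives power 0.795 with 63 and 0.801 with 64 per group, so 64. For attrition, 64/(1 − 0.19) = 79.01, so 80 per group and 160 in total. The stated figures reproduce, for SSEQ as the only primary outcome.

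**2. False-positive rate if both are primary and either suffices.** With each test at two-sided 0.05, the rate is 1 − P(|Z₁| < 1.96 and |Z₂| < 1.96). If independent, this is 1 − 0.95² = 0.0975. For correlated test statistics (bivariate normal):

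| Assumed correlation | At least one false positive | Multiple of 0.05 |
|---|---|---|
| 0 | 0.0975 | 1.95 |
| 0.3 | 0.0951 | 1.90 |
| 0.5 | 0.0907 | 1.81 |
| 0.7 | 0.0835 | 1.67 |
| 0.9 | 0.0704 | 1.41 |

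**3. False-positive rate on the other readings.** If SSEQ alone is primary, one test is made and the rate is 0.05. If both must be significant, the rate is at most 0.05.

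**4. Power if there are two primary outcomes.**

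- *Alpha split, 0.025 each.* By noncentral t with d = 0.5, power for SSEQ is 0.712 with 64 evaluable per group and 0.815 with 80. To keep 80% power, 78 evaluable per group are needed; 78/0.81 = 96.3, so 97 per group and 194 in total.
- *Both required at 0.05, assuming d = 0.5 on each and 64 per group.* At independence, power is 0.801 × 0.801 = 0.642. By the normal approximation it is 0.652 at independence, 0.697 at correlation 0.5 and 0.722 at 0.7.

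**The case against.** A reader might infer that the trial's false-positive rate nearly doubles. The document does not support that as a plain statement. It needs three conditions: both outcomes are primary, success on either is enough, and the tests are close to independent. The article contradicts itself on the first and is silent on the second. The third is the least plausible: both scales are 0-to-10 confidence ratings concerning self-management, given to the same people in the same interview, so positive correlation is likely and 9.75% is an upper value. This objection stands, and the error figures are therefore conditional.

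A reader might also treat the lack of a rule for combining the two outcomes as a fault in itself. Such a rule is commonly left to the statistical analysis plan or the full protocol, neither of which is shown, and a general significance level does not exclude one. That stands too. It does not remove the contradiction: an analysis plan could choose one definition, but it could not make these sections of the article agree.

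On power, the 71% assumes exactly 64 evaluable per group. The 19% attrition is a six-month figure while follow-up is at eight weeks, so more may be evaluable. Hence both ends, 71% and 81%, are given.

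Finally, outcome expectation is one of the two constructs on which the programme is built, so two primary outcomes may be what was intended. That is fair, and the fix allows for it.

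**Conclusion.** The contradiction is established from the text and needs no assumption: one primary outcome in the sample size section, two in the abstract, the outcome measures section and Table 3. The sample size arithmetic is sound for the single-outcome definition.

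The effect on error is conditional. If both outcomes are primary and either suffices, the false-positive rate lies between 7.0% and 9.5% for assumed correlations of 0.9 to 0.3, with 9.75% at independence. Otherwise there is no inflation.

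The 80% power is stated for SSEQ alone. With two primary outcomes it has to be restated, except in the case of an alpha split with nearly full retention, where SSEQ would keep about 81%.

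This should be settled because it decides what the trial may claim.

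**What to change.** Reconcile the sections before any unblinded analysis.

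*Preferred:* keep the sample size section's definition, with SSEQ at eight weeks as the only primary outcome. Make outcome expectation the first-ranked secondary outcome, tested at two-sided 0.05 only if SSEQ is significant. Align the abstract, the outcome headings and Table 3. The 160 participants, the 5% error rate and the 80% power then stand as written.

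*If two primary outcomes are intended:* change the sample size section instead, state the success rule (both required, or alpha split between them), and restate the power for that rule.

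*Cost:* the preferred route needs no extra patients. Outcome expectation could no longer carry a positive trial on its own. Because it removes an outcome now listed as primary, the change must be checked against the registered outcomes, which are not visible here, and may need an amendment. With two primary outcomes the cost is lower power or a larger trial: for an alpha split, 194 participants in place of 160 if 80% power and the 19% attrition allowance are kept.
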